### Outputs

The key output from this stage will be a reliable, valid and parsimonious measure of awareness in people with severe dementia that takes into account user perspectives, and which is presented in a format that can be easily used by care staff, accompanied by a comprehensive and accessible user manual.

## Stage Three: Intervention trial

### Design

In this CRT paid carers will be trained to use the new measure of awareness and the effects on resident well-being and quality of life will be evaluated. Eight care homes will be recruited to the trial. Half the homes will be randomised to receive the training intervention; the remainder will receive no additional input. Baseline assessments will be completed in pairs of homes of similar size and type (public or independent sector) before one of the pair is randomised to receive the intervention. A CONSORT-style flowchart is shown in Figure 1.

**Figure 1 F1:**
[figure not shown]
**CONSORT-style flowchart for Phase 3**.

### Participants

Stage Three will be conducted with 8 care homes which were not involved in the previous stage. We will recruit 10 residents per home giving a total sample of 80 people with severe dementia who have no, or only very limited, verbal communication.

### Measures

(a) Measures for assessment of the person with dementia

• Awareness will be assessed using the new measure.

• Severity of dementia: Functional Assessment Staging (FAST) [30].

• Cognitive functioning: Guy's Advanced Dementia Schedule (GADS) [32].

• Behaviour: Behavioural assessment scale of later life (BASOLL) [34].

• Well-being: Positive Response Scale (PRS) [28].

• Quality of life: Quality of Life in Late-stage Dementia (QUAL-ID) [29].

(b) Measures for care staff

• Staff attitudes: Approaches to Dementia Questionnaire (ADQ) [35,36]; a 19-item reliable and valid scale assessing person-centred and hopeful attitudes to people with dementia.

• Care practice: The Dementia Care Practitioner's Assessment (DCPA) [37]; an observational schedule evaluating quality of care provided by staff.

• Well-being: Maslach Burnout Inventory (MBI) [38]; a brief self-report questionnaire providing scores for emotional exhaustion, depersonalisation and personal accomplishment.

• General Health Questionnaire (GHQ-12) [39]; a brief, well-validated measure of psychological distress.

### Intervention

In the intervention condition, care staff will be introduced to the measure in teaching sessions, gain hands-on experience of using the measure under the guidance of a trainer, and then undertake observations of allocated residents and receive group supervision to support the development of care practice with those residents. An accredited trainer will advise on, and support the process of, staff training. For each home, the intervention period will last for 8 weeks. In weeks 1 - 2, two 90-minute training sessions will be provided, and each staff member involved will be given an individualised observation schedule. In weeks 3 - 8, each staff member will conduct six 10-minute observations per week and receive 30 minutes face-to-face or telephone contact with the researcher. Observations will be scheduled so that (a) pairs of staff members make independent observations of the same resident; (b) each staff member observes each identified resident on a number of occasions; (c) each staff member observes at least three different residents; and (d) each staff member observes at least two residents over an extended period of at least three weeks. Observations will be conducted in public areas of the home while the residents are awake. All staff will participate in fortnightly one-hour group supervision sessions, where they will be encouraged to consider variations in residents' level of awareness, and to identify and implement ways of supporting increased levels of awareness.

### Procedure

Participants will be assessed initially with the GADS and observed for two 30-minute sessions with the PRS, a staff member will be interviewed to obtain background information and ratings on the FAST and BASOLL and proxy ratings on the QUAL-ID, and where possible a family member will be interviewed to obtain proxy ratings on the QUAL-ID. Staff members will also complete the ADQ, MBI and GHQ-12. Care practice will be observed for 6 hours in each home using the DCPA. For homes in the intervention condition, staff will participate in the training and observational work. For homes in the usual care condition, no staff training will be provided. After 8 weeks all measures used in the initial assessment will be repeated by a researcher blind to group allocation.

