**Methods/Design:**

In Stage One, a measure of awareness in severe dementia will be developed. Two focus groups and an expert panel will contribute to item and scale development. In Stage Two observational data will be used to further develop the measure. Working in four care homes, we will recruit 40 individuals with severe dementia who have no, or very limited, verbal communication. Data on inter-rater reliability and frequency of all items and exploratory factor analysis will be used to identify items to be retained. Test-retest and inter-rater reliability for the new measure will be calculated. Correlations with scores for well-being and behaviour and with proxy ratings of quality of life will provide an indication of concurrent validity. In Stage Three the new measure will be used in a single blind cluster randomised trial. Eight care homes will participate, with 10 residents recruited in each giving a total sample of 80 people with severe dementia. Homes will be randomised to intervention or usual care conditions. In the intervention condition, staff will receive training in using the new measure and will undertake observations of designated residents. For residents with dementia, outcomes will be assessed in terms of change from baseline in scores for behaviour, well-being and quality of life. For care staff, outcomes will be assessed in terms of change from baseline in scores for attitudes, care practice, and well-being.

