### Measures for assessment of the person with dementia

• Severity of dementia: Functional Assessment Staging (FAST) [30], a widely-used brief system for categorising severity of impairment in people with dementia. [In the initial funding application we proposed to use the Global Deterioration Scale [31], but following initial piloting we decided to replace it with the FAST which provides a more fine-grained classification.]

• Cognitive functioning: Guy's Advanced Dementia Schedule [32]; a structured assessment of cognitive ability that involves measuring responses to familiar objects. [In the initial funding application we proposed to use the Severe Impairment Battery [33], but as initial piloting indicated floor effects on this measure we replaced it with the GADS.]

• Behaviour: Behavioural Assessment Scale of Later Life (BASOLL) [34]; a reliable and valid rating of self-care ability, functioning and behaviour, completed by staff.

• Well-being: Positive Response Scale (PRS) [28]; an observational scale completed by a trained rater that focuses on the person's affective response to the environment.

• Quality of life: Quality of Life in Late-stage Dementia (QUAL-ID) [29]; an 11-item scale completed by a proxy with reference to the person's quality of life in the preceding week.

• Awareness: Wessex Head Injury Matrix (WHIM) [18,19]; an hierarchical list of 62 observable behaviours, ranging from 'looks at person briefly' to 'knows the name of one staff member'. This will be modified in line with recommendations from Stage One.

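### Assessor blinding at 8 weeks does not reach BASOLL, the staff-proxy QUAL-ID or the staff self-report scales, because care staff supply those scores

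*Protocol article*

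**What the plan says.** The abstract labels the trial: "In Stage Three the new measure will be used in a single blind cluster randomised trial". The Stage Three Procedure gives the safeguard behind that label: "After 8 weeks all measures used in the initial assessment will be repeated by a researcher blind to group allocation". No other section limits it to particular measures.

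The abstract names three resident outcome domains: "outcomes will be assessed in terms of change from baseline in scores for behaviour, well-being and quality of life". Their instruments are BASOLL, PRS and QUAL-ID. On who supplies the scores:

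- BASOLL is described in the Stage Two measures list as "a reliable and valid rating of self-care ability, functioning and behaviour, completed by staff". In Stage Three, "a staff member will be interviewed to obtain background information and ratings on the FAST and BASOLL and proxy ratings on the QUAL-ID".
- QUAL-ID is "an 11-item scale completed by a proxy with reference to the person's quality of life in the preceding week". Besides the staff rating, "where possible a family member will be interviewed to obtain proxy ratings on the QUAL-ID".
- PRS is "an observational scale completed by a trained rater that focuses on the person's affective response to the environment".

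The Stage Three Procedure also has staff fill in the ADQ, MBI and GHQ-12, while care practice is observed with the DCPA.

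**The concern.** Blinding protects a score only if the person making the judgement is blind. For BASOLL and the staff QUAL-ID that person works in the home. Intervention homes have training, scheduled observations and group supervision; usual care homes have no training. Staff in either arm would therefore normally know their allocation.

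This goes further than ordinary unblinding. The intervention sets out to change how staff see residents. If a staff member comes to read the same resident differently, the score can move with no change in the resident. The Background section also describes QUAL-ID as depending heavily on the rater's interpretation.

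The Outputs section of Stage Three uses the effect size and ICC to size a definitive trial. For a given power, the required sample varies as the inverse square of the standardised effect. An effect inflated by rater shift would make that trial too small, and a reader relying on the blinding sentence would have no warning of it.

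**Working it through.** No sample-size figure is at issue. The check matches each measure in the Stage Three initial assessment to the person who supplies the score, and asks whether a blind researcher makes that score blind.

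| Measure | Who supplies the score | Can a blind researcher blind it? |
|---|---|---|
| PRS (resident well-being) | trained observer | yes |
| BASOLL (resident behaviour) | care staff, by interview | no |
| QUAL-ID, staff version | care staff, by interview | no |
| QUAL-ID, family version | family member, where available | not settled; family blinding not stated |
| GADS (cognition) | direct assessment | yes |
| FAST (severity; not a listed outcome) | care staff, by interview | no |
| ADQ, MBI, GHQ-12 (staff) | staff self-report | no |
| DCPA (care practice) | observation | yes |

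**Count, resident outcomes.** The three domains have four score sources (BASOLL, PRS, staff QUAL-ID, family QUAL-ID). One can be blinded by the stated procedure, two cannot, and one is undetermined and incomplete.

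**Count, staff outcomes.** Of four instruments, three are self-reports (ADQ, MBI, GHQ-12) and one is observed (DCPA).

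**Does change from baseline remove the problem?** The Stage Three Design section places baseline assessment before randomisation, so baseline ratings are made before anyone knows the allocation. Write the staff-rated change in each arm as true change T plus rater shift s. The between-arm contrast is

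(T_I + s_I) − (T_C + s_C) = (T_I − T_C) + (s_I − s_C).

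The shift arises between the two ratings, so subtracting baseline does not cancel it. The article says that repeated observations and ratings by staff may cause some change in control homes, which concerns the control arm. It does not address a difference in shift between arms.

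**Can the collected data show it?** In residents with both QUAL-ID versions, let f be any shift in family ratings. If staff and family register the same true change, the between-arm difference in (staff change − family change) is (s_I − s_C) − (f_I − f_C). If family shift is similar in both arms, this isolates differential staff shift. Both conditions are assumptions; the article settles neither.

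**The case against.** The blinding sentence can fairly be read as covering only the researcher who administers the measures. The same paragraph says openly which ratings come from staff, and a single-blind label is compatible with assessor blinding. This stands: the procedure is feasible and the fault is an overstated safeguard. But the sentence covers every measure without qualification, so the stronger reading is invited.

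Several stronger inferences are tempting and are not supported:

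- A reader might infer that two of the three resident outcomes are wholly unblinded. QUAL-ID also has a family version, so this is certain only for BASOLL and the staff version.
- A reader might infer that the raters are the trained staff themselves. The article says only that a staff member is interviewed. Likely knowledge of allocation is enough for the point; retraining of that particular rater is not established.
- A reader might treat the ADQ, MBI and GHQ-12 as exposed to the same false reading of residents. For these, change in staff is itself the outcome. They are unblinded self-reports, which is a lesser problem.
- A reader might put a number on the shift, or set it against the ±0.3 interval in Data analysis. The documents give no size for a shift, and that interval concerns change within either arm, not the contrast between arms. Direction is open too: staff who notice more may also report more distress.
- A reader might conclude that the PRS, or the family QUAL-ID, should become the lead outcome. The article names no lead resident outcome, its core hypothesis concerns quality of care and quality of life, and the Background says the PRS also depends heavily on rater interpretation. Family availability and blinding are unknown.

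It is also fair to say that Stage Three is preparatory and its evidence is called preliminary. That lowers the stakes for inference, but the effect size is carried forward to planning.

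**Conclusion.** The point holds as an overstated blinding safeguard. Of the resident outcomes, only the PRS is scored by an assessor who can be blind; BASOLL and the staff QUAL-ID are rated by people who would normally know their home's allocation. Three of the four staff instruments are unblinded self-reports.

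This rests on two assumptions: that staff know whether their home was trained, which follows in practice from the intervention as described, and that observers using the PRS, GADS and DCPA are kept blind while working in the homes, which the article asserts. The size and sign of any rater shift are unknown. A reader might infer that any observed effect on behaviour or quality of life would be rater shift alone; the documents show only that such a shift could not be ruled out on these scores.

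**What to change.** 1. In the Stage Three Procedure, limit the assessor-blinding statement to PRS, GADS and DCPA, and align the single-blind label in the abstract with it.
2. Label BASOLL, the staff-proxy QUAL-ID and the ADQ, MBI and GHQ-12 as unblinded wherever their results are given.
3. Report staff and family QUAL-ID change side by side by arm, in residents with both, as a check for rater shift. State that family members are not known to be blind.
4. Do not size the definitive trial on staff-rated effect sizes alone; show the PRS effect beside them.

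The cost is wording and one extra table from data already planned. The paired QUAL-ID comparison will use fewer than the 80 residents wherever no family member is available. It will be less precise, so a lack of visible divergence would not prove that there was no shift.

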### Data analysis

The data analysis will have four purposes: first, to estimate the intra-class correlations (ICC) required to power a large-scale trial; second, to conduct a confirmatory factor analysis on the developed tool in order to test the hypothesised structure which emerged from stage 2; third, to develop and test an analysis plan based on multilevel modelling; and fourth, to examine change from baseline scores on all outcome measures by randomisation group to assess possible effect size associated with both intervention and control arms (the repeated observations and ratings made by staff may trigger some changes in the control homes). A sample size of 8 care homes with 10 participants per home achieves 90% power to detect an ICC of 0.3 under the alternative hypothesis when the ICC under the null hypothesis is 0.0 using an F-test with a significance level of 0.05 [40]. The proposed sample size will also yield estimates of the standardised effect size of the change from baseline in either arm of the trial with a 95% confidence interval of +/- 0.3.

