### Outputs

The information obtained about the ICC and effect size will make it possible to determine the sample size required for a definitive, larger-scale trial. In addition, this initial RCT will supply additional information about the new measure, provide an opportunity to test the intervention in a systematic way, and allow us to gain a clear picture of the practicalities involved in implementing the research method in the care homes. Findings will be incorporated into existing training provision for care staff offered by the Bangor Dementia Services Development Centre and the Bradford Dementia Group.

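### The ±0.3 precision stated for the standardised change in either arm treats residents as independent and leaves out clustering within four homes per arm

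*Protocol article*

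**What the plan says.** The Stage Three Participants section of the protocol article sets the size: "We will recruit 10 residents per home giving a total sample of 80 people with severe dementia". The Design section allocates by home: "Half the homes will be randomised to receive the training intervention". Each arm is therefore 4 homes and 40 residents.

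The Data analysis section then makes two numerical statements in succession. The first concerns the ICC: "A sample size of 8 care homes with 10 participants per home achieves 90% power to detect an ICC of 0.3", "when the ICC under the null hypothesis is 0.0 using an F-test with a significance level of 0.05". The second says the same sample will also give estimates of the "standardised effect size of the change from baseline in either arm of the trial with a 95% confidence interval of +/- 0.3". No ICC, design effect or independence assumption is attached to the second statement.

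The same section lists estimation of ICCs as the first purpose of the analysis, and as the third "to develop and test an analysis plan based on multilevel modelling". The Outputs section says what the estimates are for: "The information obtained about the ICC and effect size will make it possible to determine the sample size required for a definitive, larger-scale trial".

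**The concern.** Residents in one home share staff, routines and raters, so their changes from baseline are likely to be correlated. The study is built around that expectation: it randomises homes, sets out to estimate the ICC and plans multilevel models. A precision figure for this design should therefore reflect both the within-home correlation and the small number of homes. The stated figure appears to reflect neither.

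This is the only precision the article gives for the effect size, and the effect size is one of the two quantities that will inform the definitive trial. Required sample size varies with the inverse square of the assumed effect. A reader who takes the pilot estimate as good to ±0.3 would therefore trust it more than the design allows.

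**Working it through.** **Inputs.** Homes per arm: 8/2 = 4 (Design). Residents per home: m = 10 (Participants). Residents per arm: n = 40. The change is standardised by its own SD, taken as 1 and known. The article gives no ICC for change scores, so the ICC is an assumption and is varied. The value 0.3 comes from the ICC power statement; the lower values are illustrative.

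**Step 1: reproduce the stated figure.** With independent residents the half-width is 1.96 × √(1/n).
- n = 40 (one arm): 1.96/√40 = 0.310, or 0.320 with t on 39 df. Both round to 0.3.
- n = 80 (both arms together): 1.96/√80 = 0.219. No match.
- Difference between arms, 40 v 40: 1.96 × √(2/40) = 0.438. No match.

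The value for 40 independent residents agrees with both the number and the description (either arm).

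**Step 2: check the neighbouring ICC statement.** For a one-way random-effects F-test with 8 homes of 10, the variance ratio at ICC 0.3 is 1 + 10 × 0.3/0.7 = 5.29. The power at the 0.05 level is 0.896, which agrees with the stated 90%. That sentence stands.

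**Step 3: allow for clustering.** The mean of an arm with 4 homes of 10 has variance DEFF/40, where DEFF = 1 + (m − 1) × ICC = 1 + 9 × ICC. The half-width is multiplier × √(DEFF/40). Three multipliers are shown:
- 1.96 (normal)
- 2.447 (t on 6 df, between-home variance pooled over both arms: 8 homes less 2 means)
- 3.182 (t on 3 df, from the 4 homes of one arm alone)

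| ICC | DEFF | Effective n per arm | Normal | t, 6 df | t, 3 df |
|---|---|---|---|---|---|
| 0.05 | 1.45 | 27.6 | 0.37 | 0.47 | 0.61 |
| 0.10 | 1.90 | 21.1 | 0.43 | 0.53 | 0.69 |
| 0.20 | 2.80 | 14.3 | 0.52 | 0.65 | 0.84 |
| 0.30 | 3.70 | 10.8 | 0.60 | 0.74 | 0.97 |

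For example, at ICC 0.3: √(3.7/40) = 0.304, and 0.304 × 1.96 = 0.60.

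**Step 4: compare with the stated value.** Relative to 0.3, the range is 0.373/0.3 = 1.2 (ICC 0.05, normal) to 0.968/0.3 = 3.2 (ICC 0.3, t on 3 df). With the normal multiplier the half-width still rounds to 0.3 only if 1.96 × √(DEFF/40) < 0.35, that is, for an ICC below about 0.03.

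**Step 5: what the narrow interval would cover.** Taking the variance as known, an interval of ±0.31 would cover about 90% at ICC 0.05, 84% at 0.10 and 69% at 0.3, instead of 95%.

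**The case against.** The strongest reply is that 0.3 is not a planning value for this sentence. It is the alternative in a test of ICC = 0, hence a value the study could detect. The article neither says that 0.3 is expected nor ties it to change scores. This stands. A reader might infer that the plan contradicts its own ICC and that the interval is really two to three times too narrow; the article does not support that as a fixed result. At ICC 0.05 to 0.10 the factor is 1.2 to 1.4 with the normal multiplier. A factor of two or more needs an ICC towards 0.3 or the 3 df multiplier, and 3 df is only one option: pooling over both arms gives 6 df.

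A second reply is that the article does not say which SD standardises the change. With the baseline SD and a baseline to follow-up correlation r, the half-width is 1.96 × √(2(1 − r) × DEFF/40). This comes to about 0.3 with clustering included at, for example, r = 0.8 with ICC about 0.17, or r about 0.87 with ICC 0.3. So independence is not the only arithmetic route to 0.3. It is, however, the only one that needs no unstated correlation, so this does not rescue the sentence.

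Third, the number of homes rests on the ICC test, which is correct, and the definitive trial would be sized from the observed estimates, not from this half-width. That limits the consequences but does not make the stated precision right. Nor should a reader infer that the reported intervals will ignore clustering, because multilevel modelling is already planned.

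Losses to follow-up add nothing material: with 32 residents per arm, 1.96/√32 = 0.35 (0.346), which still rounds to 0.3 at the precision given.

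**Conclusion.** The ±0.3 is wrong as written for this design. It is the value for 40 independent residents per arm, stated without that condition, in a trial with 4 homes per arm whose first analytic purpose is to estimate the ICC. The fault is an unstated independence assumption placed beside a sentence that considers an ICC of 0.3; it is not a proven error of one fixed size. Depending on the ICC of change and the multiplier, the half-width is about 0.37 to 0.61 at an assumed ICC of 0.05 and 0.60 to 0.97 at 0.3, or about 1.2 to 3 times the stated value.

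This rests on equal homes of 10, change standardised by its own known SD, and a common ICC in both arms. It concerns resident outcomes. Staff outcomes are clustered too, but the article gives no number of staff, so nothing can be computed for them. The ICC power statement is unaffected.

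**What to change.** Replace the ±0.3 with cluster-adjusted half-widths over a stated range of ICCs, naming the design effect, the multiplier and its df, and the SD used to standardise. Suggested wording:

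> With 4 homes of 10 residents per arm (design effect 1 + 9 × ICC), the 95% CI half-width for the standardised change in an arm is about 0.47 at an ICC of 0.05 and 0.74 at an ICC of 0.3, using t on 6 df with variance pooled over arms (0.61 and 0.97 using t on 3 df within one arm).

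State also that effect-size intervals will be taken from the multilevel model already planned. A between-arm half-width could be added but is optional. With t on 6 df and pairing ignored, it is 2.447 × √(2 × DEFF/40) = 0.66 at ICC 0.05 and 1.05 at ICC 0.3; the pairing of homes would change both the df and the variance.

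The cost is wording only. The number of homes, recruitment, measures and analysis method stay as they are; the stated precision becomes less favourable.
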